
### Objective physical activity measurement

At the time of the baseline survey, all survey participants were invited to take part in pedometer measures of physical activity. Consenting participants wore a sealed Yamax Digiwalker CW300 pedometer (Yamax Corp., Kumamoto, Japan) for the next seven consecutive days. These pedometers are valid and reliable for measuring steps in adults [72, 73] and children [74], are low cost and simple to use [75]. In 2019 we will invite all survey participants to repeat an identical 7-day pedometer protocol.

### Traffic and road user measures

At baseline and short-term follow-up (seasonally matched), traffic volume and speeds have been measured with tube counters over 7-day periods, in 8–10 locations per area. Simultaneously, pedestrian and cycle counts and road user interactions have been measured using 12-h video monitoring over 2 week days and two Saturdays. We will repeat location- and season-matched measures in 2019. A tested coding framework will be used to categorise road user interactions.

### Air quality measures

Between November 2014 and February 2015, avoiding school holidays, we undertook passive Nitrogen Dioxide (NO_2_) sampling at 28 sites in each of the intervention and control areas using Palmes diffusion tubes, a method commonly used for cost-effective air quality monitoring in NZ. NO_2_ was chosen as it is a sensitive and specific indicator of traffic-related air pollution. Sampling was repeated three times to minimise the impact of unusual traffic and weather events, and duplicate sampling was undertaken to minimise lost and outlier data. Sites for monitoring were matched to video and speed monitoring sites, with further sites representing high exposure, and some randomly allocated. Local meteorological conditions were recorded from the Māngere meteorological site. In 2019 the same monitoring protocol will be repeated, matched by date to the baseline monitoring to avoid seasonal bias.

### Population-level glucose regulation and diabetes risk

We will examine whether the intervention is associated with a shift in the population distribution of glycated haemoglobin (HbA1c) compared to the control group by obtaining an anonymised dataset of HbA1c tests taken from residents in the study areas before and after the intervention. HbA1c is considered the optimal epidemiological measure of glucose control at a population level [76], and is strongly associated with cardiovascular risk [77, 78]. In NZ, HbA1c testing is part of cardiovascular risk assessment for all men aged ≥45 years, women aged ≥55 years, and high risk groups including people with a Body Mass Index over 30, Māori, Pacific, Indo-Asian people, those with a family history of diabetes, and women with a history of gestational diabetes [79]. For those with diabetes or prediabetes the recommended frequency of HbA1c testing is at least once every 6–12 months [79]. The prevalence of diagnosed diabetes in Māngere is about 15%, and about 30% of the population meet the criteria for prediabetes [80]. The expected level of adult HbA1c testing for any year is therefore high (we estimate approximately 50%). We will match National Health Index (unique identifier) numbers over time to achieve a longitudinal sample of tests for residents of both areas. This sample of tests will include those with ‘normal’ glucose metabolism, those considered to have prediabetes (HbA1c 41–49 mmol/mol) and those with diabetes (HbA1c ≥50 mmol/mol) [79]. Accounting for increases in HbA1c with age we will chart population distributions of HbA1c, and analyse changes in mean HbA1c between areas.

### Traffic crash analysis

Survey participants have been invited to provide consent for their details to be linked to several routinely-collected data sets: the NZ Transport Agency Crash Analysis System [81] (NZTA CAS), Accident Compensation Corporation data, and the Ministry of Health National Minimum Data Set and Mortality Collection. Collectively, these datasets provide the most comprehensive data on RTIs, and avoid problems with incomplete recall of injuries by participants [82]. About 80% of baseline survey participants consented to data linkage. We will use these data to compare injury rates before and after intervention. We will also undertake analysis of routinely collected crash data at an area level using the NZTA CAS. This area-level analysis will not be restricted to survey participants or residents, as it will record all crashes and injuries occurring in the intervention and control areas. CAS generates data on crash location, severity and demographic variables. As they are rare events, pre-post changes in reported crash and injury numbers will be analysed using 5 years of pre- and post-intervention data.

### Objective safety and security scores

Previous research about neighbourhood safety and aesthetics has found mixed associations between subjective and objective measures, and called for further research measuring both [83, 84]. We undertook fine-grained street segment objective analysis at baseline using the validated NZ Systematic Pedestrian and Cycling Environment Scan audit tool [84] and Google Street View (updated every 1–3 years) in keeping with previous virtual audit research [85]. We will repeat the objective scoring of street segments in 2021, using Street View data closest to the time of the post intervention surveys. Using the same protocol, we will analyse correlation between post-intervention subjective and objective scores, and test whether there has been a significant change in either or both as a result of the intervention.

### Qualitative interviews and focus groups

In the intervention area only, face-to-face qualitative interviews were undertaken pre-intervention and early post-intervention with eight key informants who lived or worked in the neighbourhood. Interviews were conducted seated while viewing an area map, or while walking selected neighbourhood streets (‘Go-Along’ interviews [86]). Walking routes were mapped and, where relevant, photographs taken by interviewees. Semi-structured questions were used to explore perceptions of place, access to local destinations, and enablers and barriers for active transport and use of local public spaces.

In the intervention area focus groups were conducted in two primary (elementary) and one secondary school with children and young people aged 9–10 and 14–15 years, respectively. Children and young people were asked to show on area maps the routes they take to school, local shopping and recreation, places and streets they felt safe and unsafe with reasons, their mode of travel to school, local places they play and any issues locally that prevent or support them in active travel.

Data from these interviews and focus groups contributed to the intervention design. Repeat interviews and focus groups have followed the completion of the intervention, to explore residents’ perceptions of the intervention effects and add meaning to the quantitative effect measures. Thematic analysis will be used to analyse the focus groups and interviews, applying both deductive (using themes based on our causal theory) and inductive approaches.

In both the intervention and control areas, a record of major events and changes relevant to the study outcomes will also be constructed, with the aim of qualitatively assessing their impact on study outcomes.

### Statistical analysis

Data will be analysed according to area, the scale of measurement, distributional assumptions and sampling structure, accounting for the longitudinal sample as well as the cross-sectional sample. We will use separate generalised linear mixed models, adjusting for repeated measurements. If the replenishment sample is comparable to the participants lost to follow-up, we will use both sets of data in combined models, testing the sensitivity of results to our assumptions of similarity. Potential explanatory model terms and covariates in the statistical analysis will be identified a priori from our causal theory and by the use of Directed Acyclic Graphs. Because this is a complex, area-level intervention, with social components, residents living in the intervention area will be considered “exposed”, while residents living in the control area will be considered “unexposed”. In our primary analysis, we will consider exposure to be homogenous across the areas. Secondarily, we will be exploring more nuanced approaches to individual-level intervention exposure, including distance between residential address and the nearest intervention treatment.

Outcome variables to be included in analyses include: mean, median and 85% vehicle speeds, and vehicle counts by road type; changes in the mean numbers of pedestrians and cyclists seen in video data; mean reported minutes walked or cycled; mean trips walked or cycled; median weekly minutes of reported physical activity - total, recreational and transport; mean steps per day as measured by pedometer; mean perceived and objective sense of security and neighbourhood perceptions scores; self-reported and routinely recorded injuries by mode and by injury severity; changes in mean NO_2_ on different route types; and changes in mean HbA1c. Some identical questions between child and adult surveys will be analysed together, though we will also analyse child and adult survey data separately, stratify survey analyses by sex, adult age group, income, and ethnicity (including separate Pacific ethnicities), and explore differences by mobility.

### Integrated health outcomes and economic cost-benefit modelling

Our existing system dynamics modelling [13] focuses on cycling, extrapolating health and economic outcomes from changes in transport mode share and resulting physical activity, air pollution, injury, and greenhouse gas emissions. The findings from longer-term follow-up of Future Streets will enable us to refine the effect size assumptions in the model, include influences on walking, and extend the range of outcomes to include those relating to diabetes, sense of security and social connection.

We will model the theoretical impacts of wider regional or national implementation of Future Streets on population health, including, where possible, on health equity by income and ethnicity. We will use up to date economic values for outcomes to undertake cost-benefit analysis in keeping with methods already used in the transport sector [87]. We will explore the equity impacts of different scenarios for wider implementation of the Future Streets intervention. Scenarios may include: business as usual (based on current implementation patterns, which may include ‘squeaky wheel’ and ‘ad-hoc’ approaches); random (in which all areas have an equal likelihood of receiving the intervention); needs-based implementation (in which populations with the highest ‘need’ for the intervention receive additional priority); and proportionate universalism [88], in which disadvantaged social groups with lower health status receive additional priority.

## Discussion

Future Streets builds upon previous natural experiment studies assessing the impacts of transport physical environments on a range of health, social and environmental outcomes [32, 33, 35]. However, it has a number of unique strengths, including the objective measurement of a range of outcomes including physical activity. The focus on assessing interventions that may work to reduce health and social inequities is a new addition to the existing literature. The study’s controlled before-after intervention design has given the research team significant levels of control over the intervention design, area selection and implementation. The intervention was designed at an area level rather than as isolated pieces of infrastructure spread thinly over larger areas. The partnership between the research team, the community and transport planning and funding authorities meant we have been able to achieve design, funding and implementation of a transport infrastructure intervention within the constraints of a research project. The participatory intervention design brought best evidence from the literature together with crucial, context-specific community knowledge about barriers, desire lines and destinations, and local design knowledge, to develop an intervention design that has the best chance of achieving change. Control over area selection meant we have been able to match intervention and control areas on important potential confounding factors, including urban design and demographic factors.

The cross-disciplinary research team has been critical to the strong relationships with community groups and transport planners and funders, while also enabling us to develop an integrated, mixed methods plan for assessing a broader range of outcomes than has been possible in similar studies to date. In addition to breadth and comprehensiveness of outcomes, the combination of objective and subjective measures is likely to strengthen the existing evidence, and will enable triangulation between subjective and objective measures and improve validity. The broad range of outcomes will enable a comprehensive public health benefit-cost analysis of wider implementation of the intervention, rare for transport interventions.

Despite these strengths, there are significant challenges and limitations to the study. The major risks of tying a large research project to a process of design, funding and implementation of a significant amount of transport infrastructure by a local government agency, along with the challenges of this kind of collaboration, have been described already [51]. Uncertainties about the level of infrastructure funding, ability to innovate and timing of construction made it difficult to implement the study as first planned. Gradual release of funding over the period of construction meant that additional, although modest,changes to the street infrastructure have continued beyond the official date of completion. A 12-month delay in construction meant that the period between intervention completion and the first survey follow-up has been shorter than planned, and the delay is likely to have increased loss-to-follow-up among survey participants. Funding and planning limitations meant we were only able to include two areas in the study, compounding the limitations of a clustered study design. Identifying two areas that were closely matched on confounding variables meant they were close together geographically, increasing the risk of contamination, despite their severance by a motorway. Future Streets is necessarily a “realist” epidemiological study, where a balance is necessary between the recommendations of epidemiological theory, the funding available, the constraints of the transport agency and the priorities of the community.

The complexity and context-specific nature of the intervention itself make it difficult to implement elsewhere in precisely the same form. Both the process of community engagement and the physical infrastructure may play a part in any outcomes realised, while the intervention itself comprises a mixture of physical changes designed specifically for the Māngere community. We have focused on suburb level, which means that any shift from car use to active transport as a result of the intervention may be more likely to be for shorter trips within the suburb (such as trips to primary school, recreation facilities, and local shops), rather than longer habitual trips to work and higher education, although improvements in infrastructure for active transport have also improved public transport accessibility. Currently, the Future Streets cycling infrastructure is not well connected to a wider cycle network that would enable longer trips, although one early outcome of the intervention is the catalysis of discussions about wider linkages. In the meantime, this constraint may limit the size of effects across all the outcomes of interest.

Future Streets has a clustered study design, with the intervention acting at an area level, potentially undermining assumptions about observation independence and causing bias. Potential issues caused by intra-cluster dependencies include: self-selection on variables that affect outcomes, inherent differences between clusters, and external influences on one cluster but not others. In the case of Future Streets, it is unlikely that self-selection related to influences on walking and cycling have occurred before the intervention, and the intervention and control areas are well-matched on demographics, walkability and accessibility. However, with residential mobility it is possible that self-selection will be become an increasing issue as the study progresses. We have worked closely with Auckland Transport to ensure, as far as possible, that other external walking and cycling influences (especially encouragement measures) are implemented evenly across the intervention and control areas. However, it is impossible in a study like this to control all external transport factors. In addition, the intervention itself can be considered to act in two ways – through influences that are strictly individual, and through others that are “infectious” and social, including the way the infrastructure stimulates community-level activities encouraging walking and cycling. This means that controlling for intra-cluster dependencies in the analysis, while potentially reducing error, could under-estimate the true effect of the intervention, by excluding its social effects. We will therefore undertake two kinds of analysis with regard to cluster effects: one where we consider the assumptions of independence to be upheld and one where we explore the effects of violation of these assumptions*.*

Despite these considerable challenges, Future Streets offers a unique opportunity to add new and important knowledge to the urgently needed international evidence base about how we reshape cities for health, equity and environmental sustainability.

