### Outcome measures

Measures of hypothesized influences on, and outcomes of, walking and cycling are described below. The outcome measures are listed in Table 1. Short-term follow-up occurs 6–14 months following intervention completion, and longer-term follow-up will occur 2.5–3 years post intervention. Outcome measures include physical health outcomes (e.g. diabetes, injury), risk factors (e.g. physical inactivity and air pollution), social and environmental health outcomes (e.g. social connection), with a mixture of individual and area-level measures. On the basis of travel behaviour and risk factors we will model longer-term health outcomes that cannot feasibly be measured in a study of this duration. Follow-up measures are matched by month to baseline, to control for seasonal effects. Daily weather data will be included as a control variable in analyses.

**Table 1 Tab1:** Summary of Future Streets outcome measures and their timing

	2014	2015	2016	2017	2018	2019	2020	2021
*Intervention construction*		*X*	*X*					
Objective physical activity	X						X	
Road traffic injury	X					X		
Air quality measures	X					X		
Diabetes risk	X			X		X		
Vehicle speeds	X			X	X	X		
Road user counts	X			X	X	X		
Video measure of road user behaviour	X			X	X	X		
Face-to-face survey	X			X		X		
Climate pollution modelling	X			X			X	
Qualitative interviews/focus groups	X				X			
Retrospective analysis of safety and security		X						X
Health outcome and cost-benefit modelling					X		X	X

Because of the wide range of study outcomes and the paucity of previous intervention research in this area, calculating a sample size for the outcome measures was not straightforward. We were particularly interested in the objective measurement of physical activity, as a novel addition to the existing literature, and calculated sample size based on changes in steps measured by pedometry. Repeated measures sample size was based on the ability to detect a 1000 steps per day change in physical activity measured by pedometer, supported by previous research [38], with the expectation of 30% loss to follow up for survey participants. Based on these calculations, we aimed to recruit 360 child and 720 adult participants (to allow age group sub-analysis in the adult group) in each area to the survey and pedometer measures. This allowed for 80% power to detect change with a significance level of *p* < 0.05.

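### The reason given for keeping an independence analysis is wrong: allowing for area-by-period variance widens the interval and does not remove the intervention's social effects

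*Protocol article*

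**What the plan says.** The Discussion accepts that the design is clustered and that independence may fail. It lists differences between the areas and outside influences that reach only one of them among the possible causes, and concedes that not all such influences can be controlled. It then argues that the intervention works partly through social, contagious routes, so that "controlling for intra-cluster dependencies in the analysis, while potentially reducing error, could under-estimate the true effect of the intervention, by excluding its social effects". From this it concludes that two analyses are needed: "one where we consider the assumptions of independence to be upheld and one where we explore the effects of violation of these assumptions". It does not say which of the two carries the inference.

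The Statistical analysis section says: "We will use separate generalised linear mixed models, adjusting for repeated measurements". It treats every resident of the intervention area as exposed and every resident of the control area as unexposed, and in the primary analysis takes exposure to be the same throughout each area. The Setting section states that two areas were randomised, one to each condition, and that with only two areas randomisation could not balance confounders.

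**The concern.** The rationale treats an allowance for correlated outcomes as if it removed part of the effect. Where exposure is defined by area, the two are different things. The social effect belongs to the quantity being estimated; the allowance belongs to the statement of its uncertainty.

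The sentence matters because it sets in advance how the two results will be read. A reader is told that the wider, cluster-aware result may be an under-estimate, which makes the narrower independence result look like the fairer one. Yet the independence standard error gives zero variance to the threat that the same paragraph names: something that changes walking, cycling or perceptions in one area and not in the other between the survey rounds. Such an event would be counted as intervention effect, with an interval that makes no room for it. The study's effects are also meant to feed the later regional or national benefit modelling.

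**Working it through.** **Inputs from the article.** Two areas, one per arm. Outcome measures section: "we aimed to recruit 360 child and 720 adult participants" in each area, "with the expectation of 30% loss to follow up for survey participants", "ability to detect a 1000 steps per day change in physical activity measured by pedometer", power 80%, "significance level of *p* < 0.05" (taken as two-sided). After 30% loss: 360 × 0.7 = 252 children and 720 × 0.7 = 504 adults per area.

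**The plan's own figure.** No SD is given, so the target cannot be reproduced, only back-solved. With n = 2(1.96 + 0.84)²SD²/1000², n = 252 needs an SD of about 4,007 steps and n = 504 about 5,666. A one-group paired calculation needs about 5,666 and 8,013. None of this shows whether a design effect was included. The figures are used below only for the number of people per area.

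**Inputs assumed, because the article does not give them.** ICC (share of variance lying between areas at one time) 0.001 to 0.05; cluster autocorrelation CAC (correlation of an area's effect between rounds) 0.5 to 0.9; within-person autocorrelation IAC 0.5.

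**Step 1: is the social effect removed?** Write the estimate as

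D = (mean after − mean before, intervention area) − (mean after − mean before, control area).

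Its expectation is the individual effect plus the social effect, whatever correlation is assumed. For a complete cohort of m people per area,

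Var(D) = 4·ICC(1 − CAC) + 4·(1 − ICC)(1 − IAC)/m, in units of the total variance.

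The first term is the area-by-period part. It enters the variance and not the expectation.

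A simulation illustrates the same separation one level down, with streets nested in two areas and a true effect of 1000, of which 400 is social. Ordinary least squares averaged 1008 and random-intercept generalised least squares 1006 (Monte Carlo error about 6). The independence standard error was 258 against an empirical SD of 372; the model that allowed for streets gave 369. This simulation concerns street-level correlation; the area-by-period case rests on the formula above.

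**Step 2: can the data supply the area-by-period variance?** Two areas minus two arms leaves 2 − 2 = 0 degrees of freedom between areas. An area-by-period random effect is fully confounded with the intervention. Its variance must come from outside the two-area survey data.

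**Step 3: how much too narrow, post-only comparison?** Design effect = 1 + (m − 1)ICC; width factor = its square root; true error rate of the nominal 5% test = 2(1 − Φ(1.96/width factor)).

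| ICC | 504 adults: width (true alpha) | 252 children: width (true alpha) |
|---|---|---|
| 0.001 | 1.23 (0.11) | 1.12 (0.08) |
| 0.005 | 1.87 (0.30) | 1.50 (0.19) |
| 0.01 | 2.46 (0.43) | 1.87 (0.30) |
| 0.02 | 3.33 (0.56) | 2.45 (0.42) |

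**Step 4: how much too narrow, before-after cohort?** This is closer to the planned survey analysis. From Var(D), variance ratio = 1 + ICC(1 − CAC)·m/[(1 − ICC)(1 − IAC)].

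For 504 adults, ICC 0.01, CAC 0.8: 1 + 0.01 × 0.2 × 504/(0.99 × 0.5) = 1 + 1.008/0.495 = 3.04, so the width factor is 1.74.

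| ICC | 504 adults, CAC 0.5 / 0.8 / 0.9 | 252 children, CAC 0.5 / 0.8 / 0.9 |
|---|---|---|
| 0.001 | 1.23 / 1.10 / 1.05 | 1.12 / 1.05 / 1.02 |
| 0.01 | 2.47 / 1.74 / 1.42 | 1.88 / 1.42 / 1.23 |
| 0.05 | 5.25 / 3.41 / 2.51 | 3.78 / 2.51 / 1.91 |

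**Step 5: what a tipping point looks like.** An adult result with p = 0.01 under independence has z = 2.576. It loses significance when the variance ratio reaches (2.576/1.96)² = 1.73. With CAC 0.8 and IAC 0.5 that happens at an ICC of about 0.0036.

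**The case against.** Five points can fairly be made for the plan.

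- **A second analysis is planned.** A reader might infer that the study rests on the independence analysis, or that it is the only one able to give numbers. The article supports neither. It does not call that analysis primary, and an analysis over external ICC values does yield numbers and fits the stated intention to explore violation. The method may be set out in an analysis plan that is not shown, so its absence from the article is no fault.
- **The authors may mean something else by controlling.** An area-by-period fixed effect, or adjustment for social mediators measured after the intervention, would indeed absorb the effect, and less error may mean less bias. But the Discussion names neither model. For an ordinary variance allowance, which is the usual meaning, the sentence is wrong.
- **The magnitudes are assumed.** This stands. A reader might infer that every survey interval is far too narrow, or that type I error is out of control for every survey outcome. The article gives no ICC, and with a low ICC and high cluster autocorrelation the shortfall is a few percent. Replenishment also alters the figures: more people per area raises the factor, while weaker within-person correlation lowers it.
- **The risk is disclosed.** The article records differences in the delivery of other initiatives and will keep a log of major events in both areas. These help interpretation but do not change a standard error.
- **One area per arm is a design limit.** No wording removes it. The wording can still say what the interval leaves out.

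**Conclusion.** The rationale in the Discussion is wrong as written. With exposure defined by area, the between-area difference in change already contains the social effect, and an allowance for area-by-period variance widens the interval without removing that effect. The independence interval is too narrow for any positive area-by-period variance. That direction rests on no assumed value; the size does. The factor is about 1.4 to 2.5 for the adult before-after cohort at ICC 0.01 with IAC 0.5, and runs from 1.02 to 5.25 over the whole assumed range for children and adults. The analysis of violated independence remains feasible, but only with variance values from outside the two-area survey data.

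**What to change.** 1. Delete the statement that controlling for intra-cluster dependence could exclude social effects.
2. Define the estimate as the between-area difference in change, and say that it includes individual and social effects together.
3. Label the independence result as conditional on no area-by-period variation.
4. Specify the planned violation analysis: intervals for each survey outcome over a pre-set grid of ICC (for example 0, 0.001, 0.005, 0.01, 0.02) and cluster autocorrelation (for example 0.5, 0.8, 0.9), with the tipping-point value at which each result loses significance.
5. For crash outcomes only, use the year-to-year divergence between the areas in the five pre-intervention years to inform this variance. Five annual points per area are few, and they say nothing about steps, trips or perceptions.

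The cost is a change of wording and a few lines of code; no new data are needed. Intervals become wider and p-values less favourable.
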